# **Scientific rationale for study design**

# **Radiation Therapy for Benign Diseases (Including LCH and HLH) Relevance to Covid 19 Pneumonia and ARDS.**

Low dose RT has long been known to be efficacious in the treatment of several benign conditions including Graves orbitopathy, Morbus Dupuytren, and Peyronoies Disease. The use of radiation allows symptomatic relief with minimal toxicities in this cohort of patients. ^47-49,28-33^

This favorable risk/benefit ratio in these low-acuity settings justifies the consideration of RT in patients suffering from higher-acuity disease processes, for whom the potential benefits are considerably higher, and the risks are certainly no greater.

Multiple mechanisms of action have been proposed to explain the observed anti-inflammatory and anti-fibrotic effects of LDRT, including but not limited to lymphocyte depletion through ionizing damage, exudative reduction, and wavelength vibrations causing immune and pathogenic cell disruptions.^3^

Acute Respiratory Distress Syndrome (ARDS) in COVID-19 patients appears to be induced by a hyper inflammatory syndrome similar to Secondary Hemophagocytic Lymphohistiocystosis (sHLH) or Macrophage Activation Syndrome (MAS).^21^ sHLH and MAS are cytokine storm-like syndromes most commonly associated with rheumatologic disorders,^22,23^ however, viral disease in both preclinical models and in the clinical setting have been shown to induce a similar phenomenon.^24,25^ Pre-clinical data has shown CD8+ T-cell dysfunction is critical for sHLH development following a viral infection with CD8+ T-cell secreted IFN-gamma being an important mediator.^24^ Mehta et al. noted that severe COVID-19 patients have a cytokine profile similar to sHLH characterized by increased IL-2, IL-6, and INF-gamma.^21^

Lymphocytes, a main mediator of sHLH, are extremely sensitive to ironizing radiation with a D90 (dose required to reduce the lymphocyte population to 90% of initial values) of 50cGy.^50^ Fractionated radiotherapy for intracranial malignancies has been shown to induce lymphopenia.^51^ Interestingly, the data evaluating pulmonary irradiation and inflammatory infiltrates is extremely dependent on the dose and timing. Paun et al. showed increased lymphocytic lung tissue infiltration at day 1 and 7 following 1800cGy to the whole thorax.^52^ On the other hand, Zheng et al. showed that 250 cGy TBI induces a delayed pulmonary inflammatory reconstitution with a CD8+ T-cell minima at 3 days post irradiation.^53^ Importantly Zheng et al. did not show a rebound increase in lung T-cell infiltrates following RT, suggesting that a low radiation dose may be effective at transiently lympho-depleting the lungs without inducing a pro-inflammatory rebound.

The probability that lymphoid-depleting LDRT will cause clinically significant reduction in the HLH-mediated cytokine storm in COVID-19 patients is most well-demonstrated in the published outcomes of patients irradiated for other histiocytic disorders. Among these, clinical experience with LDRT for the treatment of Langerhans Cell Histiocytosis (LCH) is most robust. Researchers report exceptional response rates of over 90% of patients with LCH. Complete responses range from 76% to 93% and the majority of the rest experienced at least a partial response following LDRT in doses typically ranging from 6 to 20 Gy.^54,55^ Non-LCH are comparatively rare, among which HLH is the next most common disease and is clinically characterized by hyper-activation of ordinary macrophages and lymphocytes leading to the systemic hyper-inflammatory syndrome as discussed before.^56^We speculate that if radiotherapy is this effective in treating LCH, it might also help reduce HLH in COVID-19 patients.

# **Justification for dose**

As discussed in the introduction, single doses of 50 – 200 cGy have been used over the past decades for the treatment of inflammatory immune conditions. This is compared to nearly higher doses being used for multiple days in the treatment of cancers or histiocytic disorders. Currently doses of 70 – 150 cGy are being studied across N. America and Europe. We have selected a dose of 100 cGy for our proposed study.

# **Justification for the separate cohorts**

It is unclear as to the optimal time to intervene with LDRT in the setting of cytokine storm and ARDS. Patients having been on ventilatory for a prolonged time period may have irreversible pulmonary damage and thus not respond to the anti-inflammatory effects of a single dose of LDRT and potential suffer toxicity. We thus plan to enrol 2 distinct cohorts of patients on this study so as to separate patients who may have irreversible lung damage (prolonged ventilation) from those who not yet been placed on a ventilator. Cohort 1 will be patients who have thus far been on various non invasive O2 supplementation (e.g. nasal canula, venti-marks, rebreather mask, non-rebreather mask), and their condition does not appear to be improving or may be worsening and are at risk of requiring intubation (pre-Vent). Cohort 2 will be those patients who are already on ventilatory support for a maximum of 5 days. Each cohort will enrol independently and assessed independently.

# **Safety Monitoring**

Low dose Radiation will be administered in in accordance according to the AKUHN SOPs on administration of Radiation. The pre, during and post dose monitoring details will be captured and documented. These include:

1. Vital signs including SpO2 will be measured prior to start of LDRT and at the end of LDRT, prior to transport back to the unit and upon arrival at the unit.
2. Vital signs and clinical observation will be done hourly for the first 4h following treatment and then as per best practice clinical guidelines.
3. Safety monitoring will be done daily for the fourteen (14) day observation period.

# **End of study definition**

All eligible patients following consent will receive a single dose of LDRT within 48h of meeting eligibility and being enrolled on the study. Patients will undergo routine physical examination, vital signs and oxygenation parameters on a daily basis as part of standard of care. Observation period for the study will end on day 28 or at the time of discharge (or death), whichever comes first.

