| Description of sites/facilities enrolling patients: | 1. AKUHN – a collaborative effort of the Clinical Research Unit, Dept. of Haematology-Oncology (radiation therapy section), infectious diseases, critical care |
| Description of study intervention: | 1. Single dose of 100 cGy LDRT administered to both lungs within 48h of determining eligibility 2. Cohort 1 : 5 patients will be treated. If acute treatment related SAE is observed in ≤1 of 5 patients, additional 5 patients will be treated. 3. Cohort 2 : 5 patients will be treated. If acute treatment related SAE is observed in ≤1 of 5 patients, additional 5 patients will be treated.   If > 1 of the initial 5 patients in either cohort experiences acute treatment related SAE, enrollment to that cohort will be halted. |
| Study Duration: | 3 months |
| Participant duration: | 28d from enrollment |

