# **Schema/Schedule of events**

**Table 1:**

| **Event** | | **Responsible Personnel** | **Screening**  **(complete within 7d prior to Treatment)** | **Day 1** | **Day 2** | **Day 3** | **Day 4** | **Day 5** | **Day 6** | **Day**  **7** | **Day 14/28** | **Discharge** |
| --- | --- | --- | --- | --- | --- | --- | --- | --- | --- | --- | --- | --- |
| Informed consent^1^ | | I | x |  |  |  |  |  |  |  |  |  |
| Medical History (SOC) | | I | x |  |  |  |  |  |  |  |  |  |
| Demographics (SOC) | | CRC | x |  |  |  |  |  |  |  |  |  |
| Screening/Registration | | I/CRC | x |  |  |  |  |  |  |  |  |  |
| Eligibility Confirmation | | I/CRC | x |  |  |  |  |  |  |  |  |  |
| Ordinal Score | | I/CRC | x | x | x | x |  |  |  | x | x | x |
| Vital Signs^2^ | | CRC | x | x | x | x | x | x | x | x | x | x |
| Routine labs (CBC+ diff, lytes, LFT, Ferritin, CRP, D-dimers) | | CRC | x | x |  | x |  |  |  | x | x | x |
| Special labs^3^ (stored) | | CRC | x | x |  | x |  |  |  | x | x | x |
| Oxygenation % and setting | | CRC | x | x | x | x | x | x | x | x | x | x |
| LDRT 100 cGy (single dose) | | I (RT) |  | x |  |  |  |  |  |  |  |  |
| Adverse Events^4^ | | I/CRC |  | x | x | x | x | x | x | x | x | x |
| Concomitant Medications^4^ | | CRC | x | x | x | x | x | x | x | x | x | x |
| Data entry | | CRC | x | x | x | x | x | x | x | x | x | x |
| PI Oversight | | I | x | x | x | x | x | x | x | x | x | x |
| Data Monitoring | | CRC | x | x | x | x | x | x | x | x | x | x |
|  | ^1^Informed consent to be provided by patient, or if unable to then to be provided by next of kin (closest first degree relative)  ^2^Vital signs (temperature, blood pressure, respiratory rate, pulse oximeter) if participant experiences an AE.  ^3^Blood sample for immune profile and cytokine measurements (stored) (IL-2, IL-7, granulocyte colony stimulating factor, interferon-γ inducible protein 10, monocyte chemoattractant protein 1, macrophage inflammatory protein 1-α, and tumor necrosis factor-α, ferritin, IL-6, IL-10, IFN- α, IFN- γ) at the following time points: Day 1, 3,7, 14, 28  ^4^Particpants discharged prior to Day 14 will continue to have safety monitoring (Adverse Events and Concomitant Medications) through Day 14. This may occur as a phone call. | | | | | | | | | | | |

*Fig 1*

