# **Secondary Endpoint**

1. Efficacy - % patient able to be weaned off pre-LDRT ventilatory or oxygen support at 3d post LDRT
2. Efficacy - % patients able to come off (or avoid) mechanical ventilation within 7 days following LDRT
3. Efficacy - % patients discharged or expired at 14d/28d post LDR

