# Days 1, 3, 7, 14, and 28:

- - Ordinal Score
  - Vital Signs and Oxygenation
  - Physical exam
  - Routine labs
  - Special labs (stored)
  - Day 1 only: LDRT 100 cGy (single dose)
  - Day 1 only: Safety monitoring for 4 hours after receiving LDRT
  - Day 14 only: For participants discharged prior to Day 14, a follow-up visit/phone call for safety (adverse events and concomitant medications) will be conducted.
  - Adverse Events
  - Concomitant Medications

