# Discharge

If participant’s hospital stay is less than 28 days. If participant is discharged prior to Day 14, then monitoring for safety (Adverse Events, Concomitant Medications) will continue through Day 14:

- - Ordinal Score
  - Vital Signs and Oxygenation
  - Physical exam
  - Routine labs
  - Special labs (stored)
  - Pre-dose radiograph (Chest CT/X-Ray), per investigator discretion using the same modality as Screening, if possible
  - Adverse Events
  - Concomitant Medications

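### Deaths after Day 14 in discharged patients are not collected, although 28-day death is to be reported, and endpoint times are not mapped to study days

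*Protocol*

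**What the plan says.** The protocol sets the end of follow-up in several places, and they differ:

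- End of study definition (6.1.7): "Observation period for the study will end on day 28 or at the time of discharge (or death), whichever comes first".
- Discharge (12.4): "If participant is discharged prior to Day 14, then monitoring for safety (Adverse Events, Concomitant Medications) will continue through Day 14". The Table 1 footnote agrees that early-discharged participants "will continue to have safety monitoring (Adverse Events and Concomitant Medications) through Day 14" and allows this by phone. Section 12.2 provides the matching Day 14 visit or call.
- Safety Monitoring (6.1.6): "Safety monitoring will be done daily for the fourteen (14) day observation period".
- Synopsis, participant duration: "28d from enrollment".

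Screening (12.1) limits the later scheduled visits to the hospital stay, with the discharge procedures done once for anyone leaving before Day 28. The Day 28 visit is therefore for inpatients.

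The outcomes that need follow-up beyond discharge are time to death (secondary objective in the Synopsis and 5.1.2), the secondary endpoint on "patients discharged or expired at 14d/28d post LDR" (5.1.4), and the Statistical Analysis section (16), which summarises discharge or death by 14 and by 28 days.

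On timing, section 12.1 equates Day 1 with treatment and section 12.2 places LDRT there. The endpoints in 5.1.4 are counted in days after LDRT.

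**The concern.** There are two linked problems.

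The first is data collection. A patient discharged on Day 10 who dies on Day 20 is recorded only as a discharge: Day 20 lies beyond the Day 14 safety contact, and nothing later is scheduled. No analysis plan can recover a vital status that nobody collected. If such patients are counted as alive, 28-day mortality can be wrong in one direction only. Censoring them at last contact in a time-to-death summary is no remedy either, because discharge is itself related to prognosis.

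The second is the clock. The visit labels (Days 3, 7, 14, 28) carry the same numbers as the endpoints (3, 7, 14, 28 days after LDRT), but the labels start at 1 and elapsed time starts at 0. Without a stated mapping, different people can read the same endpoint on different days.

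**Working it through.** The protocol gives no calculated figure on this point to reproduce. The only stated size is up to 20 patients, which is 2 cohorts × (5 + 5).

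**Who is observed, and until when**

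| Patient | Last provision for contact | Unobserved up to Day 28 |
|---|---|---|
| In hospital to Day 28 | Day 28 visit (12.2) | none |
| Discharged before Day 14 | Day 14 safety visit or call (12.2, 12.4, Table 1 footnote) | Days 15–28, i.e. 14 study days |
| Discharged on Day 14 or later | discharge procedures (12.4) | discharge to Day 28 |

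Section 6.1.7, taken literally, would also remove the Day 14 contact in the second row. That is its contradiction with 12.2, 12.4 and Table 1.

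**Effect on 28-day mortality**

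In a cohort of n = 10, let d patients be discharged alive with no later vital status, and let m of them die by 28 days. Counting them as alive gives an error of −m/n, which is −10 percentage points per missed death. The worst-case bound on mortality is d/n wide:

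- d = 3: 30 points
- d = 5: 50 points
- d = 7: 70 points
- d = 9: 90 points

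These are bounds, not expected errors. The protocol gives no expected discharge rate. Its only reference is the earlier series cited in Overall design (6.1.1), at a different dose, where 9 of 10 patients left hospital within 12 days.

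The chance of missing at least one death is 1 − (1 − q)^d, where q is the probability of death in the unobserved window. The documents give no q. Assuming q between 1% and 10%:

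| d | q = 1% | q = 10% |
|---|---|---|
| 3 | 3.0% | 27.1% |
| 5 | 4.9% | 41.0% |
| 9 | 8.6% | 61.3% |

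**The visit clock**

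With LDRT on Day 1, elapsed days = study day − 1, so k days after LDRT is Day k + 1.

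| Endpoint time | Study day | Same-numbered visit is at | Available on the exact day |
|---|---|---|---|
| 24 h | 2 | – | Day 2 vital signs, oxygenation, ordinal score |
| 3 d | 4 | Day 3 = 2 d | Day 4 vital signs and oxygenation (Table 1, 12.3) |
| 7 d | 8 | Day 7 = 6 d | no study visit; daily inpatient oxygenation (6.1.7) and safety monitoring (6.1.6) |
| 14 d | 15 | Day 14 = 13 d | no study visit; routine inpatient care only |
| 28 d | 29 | Day 28 = 27 d | none; beyond the observation limit |

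If the Synopsis duration governs instead, LDRT may follow enrolment by up to 48 h (6.1.7), which leaves 28 − 2 = 26 to 28 days after LDRT. Table 1 also has no column for Days 8–13, although 6.1.6 calls for daily safety monitoring over 14 days.

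**The case against.** Several points on the other side have force.

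- A reader might infer from 6.1.7 that all follow-up stops at discharge. The documents do not support that. Adverse events are followed to Day 14 in patients discharged earlier, and a death in that time is a fatal SAE under section 7. What stands is a contradiction between sections, plus the gap after Day 14.
- A reader might infer that the 3-day and 7-day endpoints are read at 2 and 6 days. No section ties them to the Day 3 and Day 7 visits. Oxygenation is scheduled on Day 4, and daily inpatient observation covers Day 8. Of the endpoint-relevant assessments, only the ordinal score, physical examination and laboratory tests are confined to the shorter days, and no primary or secondary endpoint names them. The defect is a missing mapping.
- The 28-day endpoint can be read as a composite of discharged or expired. A discharged patient is then already classified and nothing is missing. This is fair for the composite, but it does not help time to death, or death tabulated separately.
- Missing status is not the same as a missed death. Discharge at this hospital requires resolved hypoxaemia on room air (10.1), so the risk after discharge may be low. This limits the likely size of the error but does not make the deaths observable.
- The trial is a descriptive pilot with no hypothesis test. Its primary endpoints and its cohort-expansion rule are assessed at 24 hours. This stands and lowers the severity.

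**Conclusion.** The concern holds in limited form and is a should-fix. The end-of-study definition conflicts with the Day 14 safety follow-up and with the Synopsis duration. No section contacts a discharged patient on Days 15–28. Deaths after Day 14, or after a later discharge, are therefore not observed, although they are needed for the 28-day mortality summary and for time to death.

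Each missed death understates mortality by 10 percentage points in a cohort of 10, if discharged patients are counted as alive. How many would be missed depends on discharge timing and post-discharge mortality. The documents give neither for this population, so the probabilities above are illustrative.

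A reader might also infer that the bias is largest in the pre-ventilation cohort, or that the 3-day and 7-day efficacy results are inflated. The first has no supporting figure in the documents. The second does not follow, because a gap after Day 14 cannot touch those endpoints.

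The one-day offset between visit labels and elapsed time is real, but for the 3-day and 7-day endpoints it is a question of definition. For 28 days, the endpoint falls on Day 29, after observation has ended.

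**What to change.** - Rewrite the End of study definition so that observation ends at 28 days after LDRT or at death, and align the Synopsis duration, Table 1 and its footnote, and sections 6.1.6, 12.2 and 12.4 with it. Settle at the same time how Days 8–13 are covered.
- Add a phone call at 28 days after LDRT for every discharged patient, modelled on the Day 14 call, recording vital status, readmission and SAEs.
- State, for each endpoint, the study day relative to LDRT that supplies it. Renumbering LDRT as Day 0 would do this, but a short mapping is enough.
- Say whether discharge and death at 14 and 28 days are reported separately or as a composite.

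The cost is at most 20 phone calls and small edits to Table 1 and the case report form. The larger burden is the amendment itself: ethics committee and regulator approval (17.3), and a revised consent form with re-consent of anyone already enrolled (11). No dose or treatment rule changes.

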# **ADVERSE EVENTS**

According to ICH Guideline for Good Clinical Practice, and for the purpose of this protocol, an adverse event is defined as any untoward medical occurrence in a clinical investigation subject administered pharmaceutical product, regardless of causal attribution. An adverse event can therefore be any of the following:

- Any unfavourable and unintended sign, symptom, or disease temporarily associated with these of a medicinal product whether or not considered related to the medicinal product.
- Any new disease or exacerbation of an existing disease (worsening in the character, frequency, or severity of a known condition)
- Recurrence of an intermittent medical condition not present at baseline.
- Any deterioration in a laboratory value or other clinical test that is associated with symptoms or leads to a change in the study treatment or concomitant treatment or discontinuation from Study drug.
- Adverse events that are related to protocol-mandated intervention, including those that occur prior to assignment of study treatment. (e.g. Screening invasive procedures)

A Serious Adverse Event (SAE) is any adverse event that meets any of the following criteria:

- Is Fatal
- Is Life threatening
- Requires of Prolongs inpatient hospitalization
- Is a congenital anomaly/birth defect in a neonate/infant born to a mother exposed to study drug/agent.
- Results in disability or permanent damage.

In this study all adverse events and Serious adverse events will be documented and assessed for treatment relation. The Radiation Therapy Oncology Group (RTOG) grading scale will be used to grade both acute and late toxicities; NCI CTCTAE 5.0 may be used for non-radiation related AEs. Pregnancy reporting will begin with first dose of LDRT through 6 months post-dose. The DSMC will be alerted in the event of an SAE and will meet within 24 hours. The adjudicating of the SAE causality will be performed jointly in consensus by the Principal Investigator and the DSMC.

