# **Inherent side-effects of low-dose radiation therapy are low**

# Adverse Outcomes

To date, the virus has been associated with high mortality, as well as adverse sequelae including but not limited to lymphopenia, leukocytosis, leukopenia, hypoalbuminemia, pneumonia, abnormal chest CT, acute cardiac injury, hypercoagulable state, acute respiratory distress syndrome, secondary infection, lung parenchyma destruction, diffuse alveolar damage, cardiomyopathy, brain injury, pleurisy, pericarditis, shock, and cytopenia.^1,34,35^

Lung irradiation is a well-studied treatment for both childhood and adult malignancies. Lung RT has well-established dosimetric threshold limits for the avoidance of toxicities such as radiation pneumonitis.^36,37^ Children with metastatic cancer such as Wilms tumor or Ewing sarcoma have been receiving whole-lung irradiation to doses of 1500-1800 cGy for decades, delivered in 150 cGy daily fractions over 10-13 treatments.^38^ The proposed single dose of 100 cGy proposed for our study is not expected to cause any acute or long term toxicity.

**The following are the potential organ systems affected by Covid 19, which may need special attention in the context of LDRT:**

1. *ARDS/Lung Parenchyma Destruction/Pulmonary Edema/ Pleurisy/Pneumothorax)*

Total-body irradiation (TBI) for marrow ablation is common in the setting of stem cell transplant, utilizing doses around 1200-1400 cGy, but again typically delivered in smaller fractions of 150-250 cGy per day with lung blocks to reduce pulmonary exposure.^39^ Safety parameters for single-fraction radiation therapy has, more recently, been established for palliation of lung metastases at dose ranges of around 800 cGy per single fraction for peripheral non-small lung cancers.^40,41^ Pneumonitis constraints for lung radiation treatments limit the total lung volume receiving 500 cGy to be 60% or less. The proposed single-fraction dose in this study of 100 cGy is considerably lower than any of these published lung toxicity thresholds.

1. *Cardiomyopathy/Myositis/Heart Failure/Pericarditis*

Patient with COVID-19 can develop cardiac injury diagnosed through elevated troponin levels.^1^ Evidence of this injury has been strongly correlated with mortality in initial studies of early disease cohorts from Wuhan, China.61 Mortality rates for those with underlying cardiovascular disease and elevated troponin levels is reported by numerous authors at 70%.^42,43^

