# **STUDY DESIGN**

# **Overall design**

This is a pilot Phase 1b/2 study to determine safety and feasibility of administering LDRT to the whole lung in a Covid 19 patient population who have progressed following administration of conventional therapy and are on ventilatory support or who are decompensating despite conventional therapy and are at risk of requiring ventilatory support to sustain life.

The rational basis is the effort to influence the pulmonary immune repertoire that is responsible for the cytokine storm responsible for the ARDS that leads to the need for mechanical ventilatory support in such patients. Previous experience at Emory University has been very favourable ^17^ Of the 10 patients (median age 78) who were requiring supplemental oxygen whose health was visibly deteriorating, received a single dose of 150 cGy. Patients were in and out of the RT unit within 10-15 minutes. Within 24h, 9/10 patients showed rapid improvement and were discharged within 12 days. No acute toxicity was observed (personal communication ahead of publication). In the meantime, there are 5 active trials studying the ability of various strategies of LDRT in Covid 19 patient population.

Our study determines to assess the safety and feasibility of administering LDRT in the LMIC setting in patients who may have different comorbidities than seen in the West, where extraordinarily expensive therapeutic agents may not be available, and where ventilators are in extremely short supply.

A single dose of LDRT is seen as a relatively inexpensive treatment in patients at the extreme end of the clinical spectrum of Covid 19 pneumonia (on ventilators or destined to need ventilator support).

Eligible patients will receive a single dose of LDRT of 100cGy which has been found to be safe and efficient is comparable settings. Patients will be followed for toxicity for the duration of their hospital stay with specific study related endpoints being determined at 24h, 3d, 7d, 14d, and 28d.

This will be a single arm, single dose pilot study involving 2 separate cohorts (Cohort 1: pre-Vent / Cohort 2: on-Vent). 5 patients will be initially enrolled on each cohort. If ≤ 1 patients experience an acute LDRT associated SAE, an additional 5 patients for a total of 10 will be enrolled.

Special labs will be collected from participants for future testing as biological correlates of response of progression.

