# **Data Safety Monitoring Committee (DSMC)**

A Data Safety Monitoring Committee (DSMC) composed of 3 individuals (clinician, clinical investigator, statistician) not involved in the study will be constituted that will review the outcome of each of the first 5 patients in each cohort at 24h following treatment. If >1 of the initial 5 patients experience an SAE felt to be related to LDRT by the investigator and/or DSMC, the study will be halted. If ≤ 1 patients experience a related SAE, a total of 10 patients in each cohort will be enrolled. Any SAE observed in any of the additional patients will be reported to the DSMC for review and discussion.

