Those with severe and critical disease are managed in the Intensive Care Unit in conjunction with the critical care team. Those with severe disease are offered high flow oxygen with face masks, non-rebreather masks and high flow nasal cannula when available. Monitoring is round the clock in case mechanical ventilation is required. The same laboratory monitoring as is indicated for moderate disease is carried out. Self proning is also done at this point. Management is supportive. Those requiring mechanical ventilation and intubation are managed with the ARDS protocol that has been previously in place. Organ dysfunction is managed in conjunction with specialists such as nephrologists and cardiologists. Other therapies that may be offered include full anticoagulation where thrombotic disease is suspected on the basis of rising D-dimer levels and worsening hypoxemia.

Discharge of the patients is based on resolution of hypoxaemia with ability to saturate at 94% or above on room air. Previously, two negative nasopharyngeal swabs have been required, but this is under review given the current MoH guidelines on home based isolation.

Medical management of patients at AKUHN is determined by a team of consultants, which include infectious disease, pulmonology, intensive care, hematology and others as needed. Treatment depends on clinical condition and severity of symptoms. Guidelines have recently been developed in order to standardize medical management of these patients (see Appendix ii).

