# **SAMPLE SIZE**

This is a pilot Phase 1b/2, proof of principle, study to determine safety and feasibility of a single dose LDRT for the treatment of severe Covid 19 pneumonia patients who have nearly exhausted conventional available options. Sample size is based on having sufficient patients to reasonably provide descriptive data for feasibility, toxicity and indication of efficacy:

- Cohort 1 (pre-Vent): 5 patients will be treated. If acute treatment related SAE is observed in ≤ 1 of 5 patients at 24h following LDRT, then 5 additional patients will be treated.
- Cohort 2 (on-Vent): 5 patients will be treated. If acute treatment related SAE is observed in ≤ 1 of 5 patients at 24h following LDRT, then 5 additional patients will be treated.

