**6. Criteria for definition as SAE:**

Resulted in Death

Life threatening

In-patient hospitalization or Prolongation

Persistent or significant disability

Congenital anomaly/birth defect

*If there is more than one criterion, choose the most significant one. Seriousness is a regulatory definition and should not be confused with severity.*

**7. Describe Event:** (A summary of signs and symptoms, diagnosis, treatment of event, concurrent treatment, other relevant medical history, including re-challenge details if applicable. Please include the point in the study at which the event occurred.)

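### The 5-patient safety count and primary endpoint 1 rest on a closed SAE list without a medically-important-event criterion, so a treated, non-life-threatening LDRT-related event can go uncounted

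*Protocol*

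**What the plan says.** Section 7 (Adverse Events) states: "A Serious Adverse Event (SAE) is any adverse event that meets any of the following criteria". The five criteria are fatal, life threatening, requiring or prolonging inpatient hospitalisation, congenital anomaly, and disability or permanent damage. Item 6 of the Serious Adverse Event Form in the Case Report Form appendix has the same five boxes and no box for anything else. It adds: "Seriousness is a regulatory definition and should not be confused with severity".

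The 5-patient rule uses this definition wherever it appears:

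- Section 1.1 (Synopsis): if more than 1 of the first five in either cohort "experiences acute treatment related SAE, enrollment to that cohort will be halted".
- Section 6.1.1 (Overall design): if no more than 1 "patients experience an acute LDRT associated SAE, an additional 5 patients for a total of 10 will be enrolled".
- Section 6.1.2 (DSMC): the study stops "If >1 of the initial 5 patients experience an SAE felt to be related to LDRT" in the view of the investigator and/or the committee.
- Section 15 (Sample size): five more are treated "If acute treatment related SAE is observed in ≤ 1 of 5 patients at 24h following LDRT".
- Section 17.9 (DSMC): the same count, in Cohort 1 and within 24 hours, governs opening the second cohort. The chair also approves continuing or halting.

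Primary endpoint 1 (section 5.1.3) is the percentage completing LDRT with no treatment-related SAE at 24 hours. Section 11 recruits only hospitalised patients.

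**The concern.** Safety is the primary aim, and the count of related SAEs is the only numeric safety rule. Whether an event enters the count depends on the SAE list, which fits an inpatient population poorly. During the stay nobody can newly require admission, and a congenital anomaly has no bearing on a count in the first days. An acute related event that is neither fatal nor life threatening therefore has two routes in: prolonged stay, or disability or permanent damage. Both usually call for a forecast, while sections 15 and 17.9 place the count at 24 hours. Sections 1.1 and 6.1.1 say only that the event must be acute, so an event recognised later as prolonging the stay could still count under those two.

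For respiratory worsening the forecast has some footing, because section 10.1 says: "Discharge of the patients is based on resolution of hypoxaemia with ability to saturate at 94% or above on room air". The gap is more likely to matter for non-respiratory events. An example is hypotension or an arrhythmia after LDRT that is reversed with fluid or drugs, leaves oxygenation unchanged, and is attributed to LDRT. Section 4.2.1 lists cardiac, liver, shock and blood-count effects among the "potential organ systems affected by Covid 19, which may need special attention in the context of LDRT". At stake are the completeness of the count and of the endpoint 1 percentage.

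**Working it through.** **Does the text close the gap elsewhere?**

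- Section 7 records all adverse events and assesses each for relatedness. This preserves the information but does not add to the count.
- Primary endpoint 2 (section 5.1.3) covers worsening of vital signs at 24 hours. No expansion or halting rule uses it, and a fully reversed event could be missed there.
- The SAE form has a tick-box for adverse events of special interest, but the protocol defines none and links none to the rule.
- The DSMC reviews each of the first five patients and can halt outside the count (sections 6.1.2, 17.9). This is a safeguard on the decision and does not alter the count.

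**Size.** The protocol states no toxicity rate, power or operating characteristic, so there is no figure of its own to reproduce. The rates below are assumptions, with patients taken as independent:

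- q: proportion of patients with a related event that meets a listed criterion.
- m: further proportion whose only important related event meets none, unless a reviewer calls it prolonging or permanently damaging.

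The probability of passing the count with five patients and per-patient rate p is

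P(X ≤ 1) = (1−p)^5 + 5p(1−p)^4 = (1−p)^4 (1+4p).

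As written, p = q. If half of the m events are already called prolonging, p = q + m/2. With the added criterion, p = q + m.

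At q = 2% and m = 3%:

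- p = 0.02: 0.98^4 × 1.08 = 0.9962
- p = 0.035: 0.965^4 × 1.14 = 0.9886
- p = 0.05: 0.95^4 × 1.20 = 0.9774

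The change is 0.9962 − 0.9774 = 0.0188, or 1.9 points, if none of m is already counted. It is 0.9886 − 0.9774 = 0.0112, or 1.1 points, if half is.

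At q = 2% and m = 0.5%, p moves from 0.02 to 0.025, and 0.975^4 × 1.10 = 0.9941. The change is about 0.2 points. At m = 0 it is nil.

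These are probabilities of passing the count. They are not probabilities that a cohort expands, because the chair must also approve continuation.

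**Endpoint 1 in a full cohort of 10.** The chance of at least one uncounted event at uncounted rate u is 1 − (1−u)^10, which is 0.140 at u = 1.5% and 0.263 at u = 3%. One uncounted patient moves the reported percentage by 1/10, or 10 points.

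**The case against.** The strongest reply is that little can fall through. Section 17.9 has the DSMC itself determine seriousness and relatedness for each of the first five patients in Cohort 1, section 6.1.2 has it review the first five in both cohorts, and continuing needs the chair's approval. The protocol expects almost no acute toxicity: section 4.1 names only fatigue and transient cytopenia. Section 4.2.1 lists organ systems but largely sets aside an LDRT effect on each, and some are late effects that could not enter a 24-hour count. Many treated haemodynamic events in these patients would be called life threatening. In a ventilated patient, vasopressor need falls in ordinal category 6 (section 12).

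Much of this stands, and it is why the point is minor. It does not make the list complete. A committee applying the protocol's definition has no item based on present medical importance, so two reviewers may class the same event differently.

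Three stronger readings are tempting and are not supported:

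- A reader might infer a large distortion. At q = 5% and m = 10% the probability of passing would fall from 0.977 to 0.835, about 14 points. Nothing in the protocol supports such rates.
- A reader might infer from section 10.1 that only hypoxaemia can prolong a stay. That section describes general discharge practice. It does not exclude other reasons, and it also provides for specialist management of organ dysfunction.
- A reader might infer that such events escape oversight. They are recorded, assessed for relatedness and open to DSMC review.

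**Conclusion.** The point holds as a minor defect in a definition. The SAE list is closed, the SAE form repeats it, and both the 5-patient count and primary endpoint 1 depend on it. In an all-inpatient trial, an LDRT-related event that needs intervention but is not life threatening can be left out unless someone judges that it prolongs the stay or causes permanent damage.

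The effect on passing the count is nil if no such events occur and about 1 to 2 points at q = 2%, m = 3%. Those rates are assumptions, and the documents allow no firmer figure. The existence of the gap follows from the text alone; only its size is assumed.

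**What to change.** Add one criterion to section 7 and one box to item 6 of the SAE form: *other medically important event, judged at least possibly related to LDRT, that jeopardises the participant or needs intervention to prevent one of the outcomes above*. State that transient cytopenia, lymphopenia or fatigue alone does not qualify, and that events attributed to COVID-19 alone are not captured by this item. Leave the timing, the relatedness requirement and the more-than-1-of-5 threshold unchanged.

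Limiting the item to possibly related events matters. Without that limit, many routine interventions in critically ill patients could become SAEs, each with a DSMC meeting within 24 hours (sections 7, 17.9) and a 48-hour report to the ethics committee (section 17.5). With it, the cost is one line, one tick-box, a few more reports and meetings, and no new visit or assessment. The chance of exceeding the count rises slightly: at q = 2%, m = 3%, from 1 − 0.9962 = 0.4% to 1 − 0.9774 = 2.3%. The new item still calls for judgement, but about the event's importance now and not about future length of stay.
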